## Abstract

Modern medicine relies heavily on diagnostic imaging because of its beneficial role in the healthcare chain. Imaging rates are increasing globally and are expected to continue to rise in the future. In tandem with this phenomenon is the increase in inappropriate imaging that adversely affects the provision of healthcare and increases the risks to patients. To date, effective interventions to reduce inappropriate imaging have shown conflicting results due to various underlying implementation designs and strategies. The aim of this controlled before-after study is to assess the impact of a clinical decision support system (CDSS) on appropriateness rates of X-ray cervical and lumbar spine in the emergency department (ED) compared to the existing practice without one, while also exploring associated outcomes. In this study, a CDSS will be carried out using implementation science principles to enhance evidence uptake with institutional medical board-approved imaging referral guidelines embedded. Recruited ED physicians will be allocated into control and intervention groups. The control group will continue the routine practice of “do nothing” for four months, while the intervention group will have a two-month CDSS intervention after an initial two-month routine practice of “do nothing”. The difference between the baseline and post-implementation appropriateness rate of imaging will be compared. This study will also evaluate the impact of CDSS on clinical effectiveness, cost avoidance, radiation doses, and sustainability. Findings from this before-after study will provide a rigorous, pragmatic test of the impact and effect of radiological CDSS as an evidence-based intervention to reduce inappropriate imaging in the ED.

## Introduction

Diagnostic imaging has seen significant change over time. Since Wilhelm Conrad Roentgen’s discovery of X-rays, the field has evolved with the introduction of sophisticated equipment and new diagnostic imaging techniques, with many more emerging technologies, such as artificial intelligence, that will continue to change the way we acquire and process images [1]. Modern medicine relies heavily on diagnostic imaging, with clinicians perceiving it as a high-value tool with both clinicians and patients benefiting from the diagnostic insights provided by imaging procedures [2,3]. Diagnostic imaging embedded within the healthcare system plays a multitude of roles in the healthcare chain, such as prevention, detection, and diagnosis of diseases; delivery and monitoring of therapy; prognosis; and many others [4]. Indeed, with such a multitude of roles, the use of diagnostic imaging is increasing globally and is expected to rise more in the future [2,5,6].

However, heavy reliance on diagnostic imaging raises serious concerns. Economically, diagnostic imaging is expensive especially for advanced imaging techniques such as computed tomography (CT) and magnetic resonance imaging (MRI) [7]. In light of escalating healthcare expenditures and limited resources, the continued growth and demand of diagnostic imaging is unsustainable. Furthermore, there are potential negative ramifications for patients, such as the detection of benign incidental findings requiring further unnecessary workup, resulting in unwarranted patient anxiety from the aforementioned processes [8]. More importantly, some diagnostic imaging techniques, such as X-rays and CT, involve ionising radiation, which subjects patients to additional radiation exposure, making radiation protection a crucial aspect of the practice.

There are an abundance of studies that highlight the effects of ionising radiation on the risk of cancer and mortality. A *BMJ* study found a linear increase in the relative cancer risk with increased radiation exposure, along with evidence of a steeper dose-response relationship at lower doses compared to the full dosage spectrum [9]. A separate population-based cohort study involving over 12 million South Korean youths revealed that the overall cancer incidence was higher in individuals exposed to diagnostic low-dose ionising radiation compared to those who were not exposed [10]. Similar findings were also demonstrated in other studies [11,12]. Notably, a recent study revealed that patients receiving relatively higher doses of radiation had a higher mortality rate within the first two years, with nearly one-third to half still alive a decade after exposure, potentially facing the effects of radiation [13]. These studies underscore the necessity of radiation protection for patients. Alongside these issues, low-value and/or inappropriate imaging exposes patients to a carcinogenic cancer risk that may manifest decades after exposure, a possibility that clinicians often overlook due to its seemingly distant nature [14].

Low-value and/or inappropriate imaging is prevalent, with a scoping review indicating that the percentage of low-value imaging ranged from 2% to 100% for inappropriate or unnecessary procedures [15]. Many factors, such as organisation culture, communication, competence, expectations, defensive medicine, roles and responsibilities, referral quality, and time constraints, exacerbate the problem of low-value imaging [16]. A systematic review of the cost associated with low-value imaging determined that the cumulative costs for such procedures totalled billions of dollars worldwide annually [17]. This warranted immediate attention to mitigate the growth of low-value and/or inappropriate imaging.

The emergency department (ED) is an area that has demonstrated a trend in increasing imaging usage [18–20]. Furthermore, there is growing evidence that low-value and/or inappropriate imaging is widespread in the ED. A recent study on the appropriateness of ultrasound, CT, and MRI in the ED of an urban academic centre revealed that the proportion of inappropriate imaging referrals ranged from 29.1% to 59.4%, depending on the imaging modality [21]. Similarly, in an early retrospective study in an ED in Singapore, it was found that 36.2% of the patients had inappropriate lumbar spine X-rays performed [22]. Furthermore, a 3-year study period’s data analysis revealed that every 18 eligible encounters included a low-value imaging study [23]. Simultaneously, ED physicians also reported imaging overuse in the ED as a problem, which is driven by several factors (i.e., defensive medicine, elderly patients) as illustrated in a systematic review by Tung et al [24,25].

Accordingly, various efforts have been explored to optimise diagnostic imaging in the ED [26]. Imaging referral guidelines have been identified as a tool that can facilitate optimisation of diagnostic imaging usage in the ED [26,27]. Imaging referral guidelines include those published by radiology societies like the American College of Radiology (ACR) Appropriateness Criteria (AC), the European Society of Radiology (ESR) iGuide, and the Royal College of Radiologists (RCR) iRefer, as well as those from non-radiological societies like Choosing Wisely (CW). A recent systematic review on the impact and effect of imaging referral guidelines highlighted that these guidelines increase the value of radiology in the healthcare system and improve the quality of healthcare and outcomes while reducing healthcare costs [28]. To further increase the impact and effect of these guidelines, they can be integrated with clinical decision support systems (CDSS) to facilitate point-of-care advice and feedback on imaging referral behaviour [29]. According to a recent study, the implementation of CDSS may lead to a reduction in multimodality imaging referrals and advanced imaging volume, while also reducing the effective dose per patient and carbon emissions [30]. Additionally, a systematic review on the effectiveness of CDSS for imaging of central nervous system injuries also showed a decrease in the use of CT and an increase in physicians’ adherence to guidelines [31].

Despite the positive utility of these findings from multiple studies, there is currently no requirement for physicians to consult imaging referral guidelines/CDSS prior to making imaging referrals in the Asian context. While the Protecting Access to Medicare Act in the United States mandates CDSS consultation for all advanced imaging, uptake of this evidence-based intervention (EBI) is still lacking, especially in Asia [32]. This was reflected in the systematic review by Tay et al., where the majority of the studies included were from the United States and Europe [28]. Various editorials from across Asia, including Korea, Singapore, and Taiwan, have advocated for strategies to resolve the growing problem of radiology manpower shortage, whereby one proposed solution is to reduce unnecessary imaging, which not only burdens radiologists but also the aforementioned problems [33–35].

However, barriers such as cost, stakeholders buy-in, lack of use, awareness, access, familiarity, usefulness, and motivation have hindered the uptake of EBIs like CDSS [36]. Implementation science can help address barriers and facilitate uptake of EBIs [37]. Despite the existence of numerous studies exploring the use of CDSS in clinical settings, this pragmatic controlled before-after study integrates an EBI (CDSS) developed using implementation science principles to enhance evidence uptake. The overall aim is to assess if the introduction of a CDSS will impact the appropriateness of X-ray cervical and lumbar spines in the ED compared to the existing practice without one. We will also evaluate the associated outcomes following the CDSS implementation.

Adherence to evidence-based imaging guidelinesClinical effectivenessCost avoidanceRadiation doseSustainability

Additionally, we will use a controlled before-and-after study design to help attribute observed effects to the CDSS intervention with reasonably confident conclusions.

## Methods

### Design and setting

This implementation research is designed to be a single-centre, pragmatic, controlled before-after study. The study received ethics waivers from the SingHealth centralised institutional review board (CIRB) (CIRB Ref: 2020/2941). Consent was waived by the ethics committee.

The study will take place in the largest tertiary hospital in Singapore, which receives an ED attendance rate of approximately 120,000 annually. The ED provides comprehensive 24-hour emergency medicine (EM) services for a wide range of emergencies, including major trauma. It offers direct access to 24/7 laboratory and diagnostic imaging services. The ED care team is comprised of EM specialists (associate consultants and above) and non-EM specialists (residents, medical officers, resident physicians, etc.).

### Characteristics of participants

A purposive sample of junior ED physicians will be approached via the ED Trauma lead. Inclusion criteria will include non-specialist EM physicians, and exclusion criteria will include non-specialist ED physicians who are unable to commit to the study period of 4 months (i.e., rotating/posting out of the ED within the study timeframe). Only non-specialists ED physicians will be recruited as they are the primary care providers for most of the ED patients and also account for the majority of the X-ray imaging referrals from the ED. Additionally, they are mostly assigned for clinical duty in the P3 and P4 sections of the ED (patient acuity category status P3: ambulant patients with minor emergencies and P4: non-emergency cases), where a substantial volume of X-ray cervical and lumbar spine are requested [38]. Notably, a previously conducted study in the same ED revealed that non-specialists accounted for a greater proportion of inappropriate orders as compared to specialists [22]. Consequently, this navigated us from the pitfall of recruiting physicians with a low baseline percentage of inappropriate imaging requests, which limits the potential for reduction [39].

This study will not employ randomisation or blinding due to its pragmatic design. The research team will take informed consent verbally prior to the study’s commencement, following an introduction and briefing.

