**Fig 1 pone.0336801.g001:**
[figure not shown]
Flow chart and timeline of the study.

In the first phase for both groups, ED physicians will follow the usual clinical practice (“Do nothing”) of making imaging referrals without consulting CDSS. Both groups will be informed during their onboarding on the availability of imaging referral guidelines in the training handbook and also on the intranet. Specifically, the physicians in the control group will not receive any CDSS introduction/orientation and no additional imaging referral guidelines education beyond the standard onboarding process. Simultaneously, a retrospective analysis of the electronic medical records will be performed.

The study included consecutive patients referred to the ED’s radiology department for cervical and lumbar spine radiography by the cohort of recruited ED physicians. Patients who had imaging referrals from general practitioners will be omitted due to our lack of access to the clinical notes for this particular cohort. For each case, the initial clinical diagnosis (reasons for the referral), the ordered procedure, patient demographics (age and gender), and ED clinical notes will be collected. To enhance the accuracy of analysing each imaging referral, the initial clinical diagnosis will be integrated with the corresponding ED clinical notes, including signs, symptoms, clinical examination, and red flags. This integration will result in a more comprehensive “indication(s)” for the imaging procedure. The appropriateness of each imaging referral will be determined with reference to localised and institutional approved imaging referral guidelines built on imaging referral guidelines published by ACR, ESR and RCR (Refer to Table 1). The records will be archived to REDCap (Research Electronic Data Capture) hosted by SingHealth for subsequent analysis.

**Table 1 pone.0336801.t001:** Imaging referral guidelines* for X-ray Cervical and Lumbar Spine.

Procedure	Clinical condition	Appropriate Imaging Criteria

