X-ray Cervical Spine	Acute trauma	1. Patient age is > 65 years old 2. Patient GCS score <15 3. Patient is intoxicated 4. Patient has midline spinal tenderness 5. Presence of focal neurological deficit 6. Presence of paraesthesia in extremities 7. Patient is unable to actively rotate neck left and right to 45 degrees 8. Not possible to test range of neck movement during patient assessment 9. Presence of dangerous mechanism of injury – fall from >1 meter/5 stairs 10. Presence of dangerous mechanism of injury – axial load injury 11. Presence of dangerous mechanism of injury – high speed motor vehicle accident 12. Presence of dangerous mechanism of injury – rollover motor vehicle accident 13. Presence of dangerous mechanism of injury – motor vehicle accident with ejection 14. Presence of dangerous mechanism of injury – motorised recreational vehicles 15. Presence of dangerous mechanism of injury – bicycle collisions
	Non-traumatic neck pain	1. Patient has history and/or current malignancy 2. Patient has prior cervical spine surgery 3. Presence of symptoms for spinal cord injury 4. Patient is suspected to have an infection 5. Patient has history of IV drug use 6. Patient has systemic disease including spondyloarthritis and diffuse idiopathic skeletal hyperostosis 7. Presence of intractable pain despite therapy 8. Patient has tenderness to palpation over a vertebral body 9. Presence of neurological deficits 10. Presence of radiculopathy 11. Presence of neck pain
X-ray Lumbar Spine	Low back pain (LBP)	1. Patient age is > 65 years old 2. Patient is osteoporotic 3. Patient has chronic steroid use 4. Patient has low velocity trauma 5. Patient is suspected to have metastatic disease 6. Patient is suspected to have an infection 7. Patient is immunosuppressed 8. Patient is a surgical candidate with persistent or progressive symptoms during or following 6 weeks of conservative management 9. Patient has prior lumbar surgery with new or progressive symptoms or clinical findings 10. Patient has trauma of dangerous mechanism

*Approved by Institution’s Medical Board.

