Briefing slides and an introduction/orientation to the CDSS will be provided to ED physicians utilising the CDSS prior to the start of this second phase (Phase 2). The briefing slides will be curated by the vendor project manager and the principal investigator (PI) and subsequently be reviewed by the senior ED physicians for comprehensibility to ensure that the materials are well-defined and well-understood. Similarly, both the project manager and the PI will blueprint a 15-minute content plan for the introduction/orientation. The introduction/orientation will be conducted virtually by the research team members and the project manager assigned to the implementation. Topics covered include: (1) introduction to CDSS; (2) user workflow; (3) orientation of the CDSS input screen; (4) orientation of the CDSS guidelines screen; and (5) orientation of the CDSS recommendation screen. There will be no evaluation at the end of the introduction/orientation, but time will be dedicated for questions and answers. While no criteria for physician learning are available, it was deemed that the most effective learning for the time-constrained physicians was self-directed through the curated briefing slides, which will be disseminated through email and WhatsApp group.

The physicians will select pre-defined clinical history from the CDSS for imaging recommendations, and they will have the option to either follow or disregard them. We will study the referral practices of the recruited ED physicians in the intervention group over a consecutive period of two months. While ED physicians are not constricted by guidelines, during the study’s second phase, there will be special strategies to improve compliance and to motivate the physicians to adhere to the guidelines. This includes email reminders and the emphasis on the audit process.

The evaluation process in Phase 2 will mimic the pre-implementation evaluation process (Phase 1) to ensure comparable results and data. Essentially, we want to conduct a careful review of the difference between the baseline and post-implementation results. The analysis will include all participating physicians in an intention-to-treat fashion.

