#### Outcome 1: Adherence to evidence-based imaging guidelines.

The primary goal is to determine the impact of the CDSS on adherence to evidence-based imaging guidelines in terms of the appropriateness rates of imaging for cervical and lumbar spine X-rays.

For both groups (“Do nothing” and CDSS), we will compare pre-implementation data on the appropriateness of spine imaging referrals with post-implementation data of the same duration (2 months). Multiple readers will evaluate each clinical indication for appropriateness using the local set of diagnostic imaging referral guidelines, with disagreement resolved by consensus.

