### Data and statistical analysis

We will describe participant and patient demographics, clinical and imaging characteristics, and study outcomes using standard methods, such as frequencies and percentages for categorical variables and mean, standard deviation, median, and range for continuous variables.

We will use a t-test to examine the outcomes before and after the intervention (“Do nothing” and CDSS). The primary outcome (appropriateness) is binary at the patient level but analysed at the physician (cluster) level. Each physician’s mean appropriateness in the pre- and post-phases will be compared using a paired t-test on within-physician differences; if assumptions of normality are materially violated, analyses will be repeated with a variance-stabilising transformation.

To complement this, patient-level multilevel logistic regression models will be performed with a random intercept for physician and fixed effects for phase, intervention arm, and their interaction. Patient-level (age, sex, indication type) and physician-level (specialty) covariates will be included to adjust for potential confounding. Both unadjusted cluster-level and adjusted multilevel estimates will be reported side by side. Where possible, we will present all effects with confidence intervals.

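### Blinding is waived for the whole study on grounds of pragmatism, but that reason does not cover the readers who judge appropriateness from archived records and so determine the primary endpoint

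*Protocol article*

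**What the plan says.** Under Characteristics of participants, the protocol article says: "This study will not employ randomisation or blinding due to its pragmatic design". It makes no exception for outcome assessors there or elsewhere.

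Appropriateness is determined by record review. Under Comparator and intervention, while Phase 1 is under way, "Simultaneously, a retrospective analysis of the electronic medical records will be performed", and Phase 2 follows the same evaluation process. For each case, "the initial clinical diagnosis will be integrated with the corresponding ED clinical notes, including signs, symptoms, clinical examination, and red flags". Outcome 1 then says: "Multiple readers will evaluate each clinical indication for appropriateness using the local set of diagnostic imaging referral guidelines, with disagreement resolved by consensus". The Data and statistical analysis section confirms that this verdict is the endpoint: "The primary outcome (appropriateness) is binary at the patient level but analysed at the physician (cluster) level".

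Other relevant statements:

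- Groups are formed by the physician's posting date (Comparator and intervention).
- The CDSS is standalone and sits outside order entry (same section).
- The principal investigator helps prepare the CDSS briefing slides (same section) and performs the analysis (Safety considerations).
- The Limitations discuss baseline imbalance, the Hawthorne effect, gaming, selection and history. They do not discuss assessor bias.

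**The concern.** The stated reason and the scope of the waiver do not match. Physicians cannot be blinded to a tool they are asked to use. Readers of stored records can be, because nothing in a retrospective review requires them to know when the X-ray was ordered or by whom.

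The endpoint is a judgement, and without randomisation the design has few other protections. If readers know that a record comes from the CDSS post-phase and expect improvement, a lenient reading of borderline cases goes directly into the primary effect. The existing safeguards do not remove this. Consensus among readers who share the same knowledge can preserve a shared expectation. The control group does not cancel it either, because readers who know the group can be lenient in one cell only.

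The verdict is also reused. Outcome 3 multiplies the number of inappropriate examinations by cost, and Outcomes 2 and 4 split positivity and dose by appropriate versus inappropriate.

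**Working it through.** **1. Where readers have discretion (Table 1).**

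- *Lumbar spine:* suspected metastatic disease; infection ("Patient is suspected to have an infection"); persistent or progressive symptoms in a surgical candidate; and trauma of dangerous mechanism, which this list does not define.
- *Cervical spine, sorting step:* neck pain alone qualifies a non-traumatic referral but is not an acute-trauma criterion. Classing a case as traumatic or non-traumatic can therefore change the verdict.
- *Little or no discretion:* age, GCS and prior surgery are factual. Cervical dangerous mechanisms are itemised. Within the non-traumatic neck list, intractable pain and suspected infection cannot change a verdict, because neck pain already qualifies.

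**2. The plan's own figure (Sample size).** Inputs: standardised effect 0.3, alpha 0.05, power 0.90.

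- Normal approximation, two-sided: n = 2(1.960 + 1.282)²/0.3² = 233.5, so 234 per group and 468 in total.
- The exact independent-samples t-test gives 234.46, so 235 per group.

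Both stated numbers are reproduced. One-sided testing (191 per group) and a paired t-test (119 pairs) do not match them.

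**3. Illustration of reader bias.** Inputs: 20% inappropriate and 235 per phase (Sample size), so 0.20 × 235 = 47 inappropriate referrals per phase. Assume no true change. Let f be the share of inappropriate post-phase referrals that are read as appropriate. The share f is an assumption; the article gives no value.

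With p₁ = 0.20, p₂ = 0.20(1 − f) and p̄ their mean:

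- SE₀ = √[2p̄(1 − p̄)/235]
- SE₁ = √{[p₁(1 − p₁) + p₂(1 − p₂)]/235}
- P(significant in favour of the CDSS) = Φ{[(p₁ − p₂) − 1.96·SE₀]/SE₁}

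Example, f = 0.20: p₂ = 0.16, SE₀ = 0.03544, SE₁ = 0.03539, and Φ[(0.04 − 0.06947)/0.03539] = Φ(−0.83) = 20.3%.

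| f | Post-phase rate | Recoded of 47 | Significant, either direction | In favour of CDSS |
|---|---|---|---|---|
| 0 | 20% | 0 | 5.0% | 2.5% |
| 5% | 19% | 2.4 | 5.9% | 4.6% |
| 10% | 18% | 4.7 | 8.6% | 8.0% |
| 20% | 16% | 9.4 | 20.4% | 20.3% |
| 30% | 14% | 14.1 | 40.9% | 40.9% |
| 40% | 12% | 18.8 | 65.8% | 65.8% |
| 50% | 10% | 23.5 | 86.1% | 86.1% |

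**4. Two reference points.**

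- With observed counts of 47/235 before, recoding 16 of the 47 after (34%) gives 31/235 and p = 0.047 by t-test.
- To produce the whole planned effect takes more. The article does not express 0.3 as a change in percentage points. Read as Cohen's h, it is a fall from 20% to about 9.5%, so (20 − 9.5)/20 ≈ 52% would have to be recoded. Read as 0.3 × √(0.2 × 0.8) = 0.12, it is a fall to 8%, so 12/20 = 60%.

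**5. Limits.** The table treats referrals as independent and uses a two-proportion test. The planned primary analysis is a paired t-test on physician means, and the number of physicians is not given, so the rates under that test cannot be computed from the article.

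**The case against.** The strongest reply is that reader knowledge is inferred. The waiver stands in a section on physician recruitment and consent and can be read as being about physicians. The description of the readers says nothing either way, the list of items collected per case does not include phase, group or physician, and data are coded. This part stands. Awareness is plausible, given the blanket wording, review alongside Phase 1 and allocation by posting date, but it is not stated. The waiver is nevertheless a decision in the text with no exception, so it is not merely detail left to a fuller document.

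Second, a fixed checklist, several readers and consensus narrow the room for bias. This also stands: discretion is mainly in some lumbar items and the neck sorting step. It is reduced, not removed.

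Third, a reader might infer that unmasked reading could produce the whole planned effect, or that it contaminates every outcome. The article does not support either. The whole effect would need more than half of inappropriate referrals recoded. Outcome 5 rests on imaging volume and tests avoided. In Outcome 4 the count of avoided imaging comes from physicians following the CDSS, so only the appropriate/inappropriate split of dose is exposed. In Outcome 2 positivity comes from radiology reports under a set definition, so only the stratification is.

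**Conclusion.** The point holds as a poorly justified design choice. Pragmatism does not support leaving readers of archived records unmasked, and their judgement is the primary endpoint. The bias is possible, not shown. Under the assumptions stated (20% inappropriate, 235 independent referrals per phase, no true effect), lenient reading of 5%, 20% or 30% of inappropriate post-phase referrals would raise the false-positive rate from 5% to about 6%, 20% or 41%. A small degree of leniency therefore does little, while a moderate degree matters. The actual degree is unknown, and clustering by physician is ignored. Exposure extends to Outcome 3 and to the appropriate/inappropriate splits in Outcomes 2 and 4, but not to Outcome 5. Masking would leave the sample size unchanged.

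**What to change.** Under Characteristics of participants, replace the blanket waiver with: physicians unblinded; appropriateness readers masked to group, phase and physician. Under Outcome 1, add how this is done:

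- Give readers the referral, notes and age without dates, physician identifier or group.
- Remove obvious mentions of the CDSS where feasible.
- Issue records in an order mixed across phases and groups.
- Unmask only after the consensus verdicts are locked.

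Records are already held in REDCap and the CDSS is outside order entry, so this looks practicable and needs no extra readers. The costs are real but small. Redacting free-text notes is partly manual, and some notes may still reveal CDSS use. Mixing the order also delays reading: Status and timeline ends data collection on 30 November 2025 and all analysis on 31 December 2025, so fully mixed reading, consensus and analysis must fit into about one month.
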